## Abstract

**Background:**

Non-technical skills (NTS), such as communication and professionalism, contribute to the safe and effective completion of procedures. NTS training has previously been shown to improve surgical performance. Moreover, increases in NTS have been associated with improved clinical endoscopic performance. Despite this evidence, NTS training has not been tested as an intervention in endoscopy.

**Objective:**

The aim of this study is to evaluate the effectiveness of a simulation-based training (SBT) curriculum of NTS on novice endoscopists’ performance of clinical colonoscopy.

**Methods:**

Novice endoscopists were randomized to 2 groups. The control group received 4 hours of interactive didactic sessions on colonoscopy theory and 6 hours of SBT. Hours 5 and 6 of the SBT were integrated scenarios, wherein participants interacted with a standardized patient and nurse, while performing a colonoscopy on the virtual reality (VR) simulator. The NTS (intervention) group received the same teaching sessions but the last hour was focused on NTS teaching. The NTS group also reviewed a checklist of tasks relevant to NTS concepts prior to each integrated scenario case and was provided with dedicated feedback on their NTS performance during the integrated scenario practice. All participants were assessed at baseline, immediately after training, and 4 to 6 weeks post-training. The primary outcome measure is colonoscopy-specific performance in the clinical setting.

**Results:**

In total, 42 novice endoscopists completed the study. Data collection and analysis is ongoing. We anticipate completion of all assessments by August 2017. Data analysis, manuscript writing, and subsequent submission for publication is expected to be completed by December 2017.

**Conclusions:**

Results from this study may inform the implementation of NTS training into postgraduate gastrointestinal curricula. NTS curricula may improve attitudes towards patient safety and self-reflection among trainees. Moreover, enhanced NTS may lead to superior clinical performance and outcomes in colonoscopy.

**Trial Registration:**

Clinicaltrial.gov NCT02877420; https://www.clinicaltrials.gov/ct2/show/NCT02877420 (Archived by WebCite at http://www.webcitation.org/6rw94ubXX NCT02877420)

## Introduction

Simulation-based training (SBT) in gastrointestinal (GI) endoscopy improves clinical performance among trainees [1-3]. However, the components of optimal simulation curricula are unclear. In procedural settings like surgery, the teaching of non-technical skills (NTS) has been shown to improve novice surgeons’ performance [4]. Despite this evidence, the impact of NTS training on endoscopy performance has not been explored.

NTS, such as teamwork, communication, situational awareness, and decision making, are important factors in healthcare regarding adverse health outcomes. A recent systematic review of critical incidents in intensive care units found that failures in non-technical domains contributed to a large proportion of medical errors [5]. Another systematic review found that deficiencies in NTS were associated with decreased technical skill in surgical settings [6].

Given the importance of these skills, several interventions have been proposed to enhance NTS among physicians. First, didactic training has been shown to improve attitudes and awareness of NTS. In a study among surgical residents, a curriculum featuring didactic teaching of NTS led to improved non-technical specific performance in the operating room, compared to conventional training (ie, daily activities on surgical wards, call schedules, and designated operating room time) [4]. Second, checklists have been shown to improve NTS, such as promoting adherence to procedural protocols, especially during surgical crises [7]. Finally, debriefing and feedback by expert instructors can allow trainees to acquire and consolidate relevant NTS. Among residents, both oral and videotape-assisted feedback can yield superior NTS acquisition compared to no feedback [8].

In endoscopy, improvement of NTS in the simulated setting is associated with superior colonoscopy skills [3]. However, the direct impact of NTS-specific training on clinical performance is unknown. This study aims to evaluate the impact of NTS training on clinical colonoscopy performance among novice endoscopists.

## Methods

This single-blind, parallel group, randomized controlled trial (RCT) is being conducted at a tertiary-care academic center. Research ethics approval was granted by the St. Michael’s Hospital Research Ethics Board (15-164). Recruitment for the study is complete. All testing and training took place at St. Michael’s Hospital ([name]). Informed written consent was acquired from all participants and patients involved in the study. The study design is summarized in Figure 1.

### Participants

A total of 42 postgraduate trainees enrolled in general surgery, adult gastroenterology, and internal medicine programs at the University of Toronto were recruited through purposive sampling. Participants were identified from a list of trainees rotating through the gastroenterology service at St. Michael’s Hospital and emailed with recruitment details. Study enrollment took place from June 2015 to June 2016. Participants were excluded if they performed 25 or more real or simulated endoscopic procedures at the time of their participation in the study.

### Simulation Devices

#### Bench Top, Low-Fidelity Simulator

The low-fidelity simulator is a validated bench-top endoscopy simulator that helps develop general endoscopic skills [9]. The simulator is comprised of a series of vertical wooden barriers with numbered holes conforming to 27 different sequences of varying complexity. An Olympus PCF-180 pediatric videocolonoscope (Olympus Canada) is used to navigate the defined sequences as quickly and accurately as possible, with visual output being displayed on a video monitor.

#### Virtual Reality, High-Fidelity Simulator

The high-fidelity simulator is the EndoVR endoscopy simulator (CAE Healthcare Canada). It models navigation through a colon, using a specialized endoscope that is inserted into a computer-based module with a screen showing the colonic lumen of a virtual patient. It provides both visual and haptic feedback related to the procedure. The VR simulator has several standardized case-based scenarios of varying complexity for colonoscopy.

**Figure 1 figure1:**
[figure not shown]
Study design.

### Experimental Design

#### Baseline Questionnaire

A written questionnaire is administered to all participants at the start of the training to collect demographic and background information including age, sex, level of training, previous endoscopy experience, and nature of experience (if applicable). Previous experience with team sports and video games is also assessed, as these activities correlate with NTS and baseline endoscopic skill, respectively (Multimedia Appendix 1) [10].

#### Pre-Test

Participants take part in a pre-test designed to assess their baseline (1) knowledge of colonoscopy (knowledge test); (2) technical skills (VR simulation test); and (3) NTS (VR simulation-based “integrated scenario” test). No feedback is provided at any point during the pre-test.

The knowledge test is a 30-minute test containing 20 multiple choice questions (MCQ) designed to assess participants’ theoretical knowledge of colonoscopy, including indications, sedation, safety, findings, pathology, and follow-up (Multimedia Appendix 2).

Participants' baseline endoscopic technical proficiency is assessed through the completion of a colonoscopy procedure on the VR simulator (EndoVR Colonoscopy Module 3). This scenario simulates a screening colonoscopy, without the need for any type of intervention, such as biopsy. There is a time limit of 30 minutes per procedure. An expert rater assesses performance, but does not provide assistance. Participants are videotaped to obtain performance measures with their faces hidden to ensure anonymity. Prior to starting the procedure, participants complete a questionnaire to measure their self-efficacy.

Following the simulator-only test, participants complete an integrated scenario format test to assess their baseline endoscopic non-technical proficiency. The integrated scenario requires participants to perform a colonoscopy procedure on the VR simulator while interacting with an endoscopic nurse and a standardized patient (SP) [11]. The simulated procedure mimics the setup of an endoscopic suite with the VR simulator positioned next to a patient table. An SP, who receives instructions regarding their medical role, acts out a scenario on colon cancer screening. Trainees are expected to explain the colonoscopy procedure, its benefits and risks, and obtain procedural consent. Trainees then carry out the procedure on the VR simulator (EndoVR Polypectomy Module #3) while responding to the patient and interacting with the standardized nurse (SN), as appropriate. The SP acts out cues from the VR simulator when the simulator signals that the procedure has exceeded its threshold for discomfort. The performances of all participants are videotaped in a similar manner to the VR simulation test to obtain performance measures. Participants are given a maximum of 45 minutes to complete the procedure. Prior to starting the procedure, participants complete a questionnaire to measure their self-efficacy.

#### Training Intervention

Participants are subsequently randomized using a randomization algorithm to 1 of 2 groups (control and intervention), following a 1:1 allocation distribution.

The control group receives 4 hours of interactive, small-group, didactic and hands-on sessions on the theory of colonoscopy, led by an expert academic gastroenterologist. The core curriculum was designed based on the American Society for Gastrointestinal Endoscopy (ASGE) colonoscopy curriculum and a detailed endoscopic training textbook and includes teaching on anatomy, pathophysiology, indications, risks and benefits of the procedures, training on specific elements of performance of colonoscopy procedures (eg, one-handed steering), and strategies for loop reduction, terminal ileal cannulation, and adequate visualization of mucosa [12,13]. This curriculum has been shown to be effective when compared to self-regulated learning on the simulator [3]. The sessions are interlaced with 6 hours of expert-assisted instruction on both the low-fidelity simulator (1 hour) and on the high-fidelity VR simulator (5 hours). Six modules of increasing difficulty in colonoscopy and colonoscopy polypectomy are taught with one-on-one feedback from an expert academic endoscopist. The endoscopy instructor demonstrates techniques, answers questions, and provides individualized performance feedback on global performance. The final 2 hours spent on the high-fidelity scenario use the integrated scenario, which features an SP and SN.

The intervention (NTS) group receives the same first 3 hours of interactive, small-group, didactic and hands-on sessions as the control group. The 4th hour of didactic sessions focuses on NTS, which includes a discussion of the major areas of NTS. Participants also watch a video demonstrating an ideal endoscopic procedure (ie, benchmark video) in terms of technical and NTS. These sessions and the video introduce trainees to the Endoscopic Non-Technical Skills (E-NTS) Checklist, which is provided for them to use during the integrated scenario training (Multimedia Appendix 3). This checklist was developed per evidence-based recommendations and targets NTS in endoscopy [14]. The NTS group also receives 6 hours of expert-assisted instruction on both the low-fidelity simulator (1 hour) and on the high-fidelity VR simulator (5 hours). Six modules of increasing difficulty in colonoscopy and colonoscopy polypectomy are taught with one-on-one feedback from an expert academic endoscopist. The endoscopy instructor demonstrates techniques, answers questions, and provides individualized performance feedback on global performance with a focus on NTS. Similar to the control group, the final 2 hours spent on the high-fidelity scenario use the integrated scenario. Terminal feedback dedicated to NTS is given after each integrated scenario by the instructor. Finally, participants in this group have access to the E-NTS Checklist during training in the integrated scenario, as participants can view the checklist prior to and after each case.

#### Post-Test

A post-test is administered after completion of the training period to compare skill and knowledge acquisition between the control and intervention groups. The immediate post-test is designed to evaluate trainees’ (1) knowledge acquisition (knowledge test); (2) technical skills acquisition (VR simulation test); and (3) NTS acquisition (VR simulation-based integrated scenario test). No feedback is provided during the post-test.

Participants’ knowledge acquisition is evaluated using the same MCQ test conducted at baseline. Again, trainees have 30 minutes to complete the 20 questions.

Participants' technical skill acquisition is assessed through the completion of the same colonoscopy procedure on the VR simulator (EndoVR Colonoscopy Module 3). The time limit is 30 minutes. Prior to starting the procedure, participants complete a questionnaire to measure their self-efficacy.

Participants' NTS acquisition is assessed using the integrated scenario procedure on the VR simulator (EndoVR Polypectomy Module #3), while also responding to the patient and interacting with the nurse, as appropriate. The time limit is 45 minutes. Prior to starting the procedure, participants complete a questionnaire to measure their self-efficacy.

#### Delayed Testing

A delayed-test is administered 4 to 6 weeks after completion of the training period to compare retention and transfer of skill between the control and intervention groups. It consists of (1) a knowledge test; (2) a VR simulation test; (3) a VR simulation-based integrated scenario test; and (4) a patient-based transfer test.

Participants’ knowledge acquisition is evaluated using the same MCQ test conducted at baseline and during the post-test. Trainees have 30 minutes to complete 20 questions.

Participants' technical skill acquisition is assessed through the completion of the same colonoscopy procedure on the VR simulator (EndoVR Colonoscopy Module 3). The time limit is 30 minutes. Prior to starting the procedure, participants complete a questionnaire to measure their self-efficacy.

Participants' NTS acquisition is assessed using the integrated scenario procedure on the VR simulator (EndoVR Polypectomy Module #3), while also responding to the patient and interacting with the nurse, as appropriate. The time limit is 45 minutes. Prior to starting the procedure, participants complete a questionnaire to measure their self-efficacy.

Participants’ transfer of skills to the clinical setting is assessed using live colonoscopies. Each participant completes 2 colonoscopies on real patients 4 to 6 weeks after the training period. These procedures are videotaped in a manner that anonymizes the participant and patient. Procedures on patients with a history of colonic or pelvic surgery or difficult colonoscopy are excluded. Sedation and monitoring are carried out per standard practice at the endoscopy unit. An experienced attending endoscopist (greater than 1000 completed procedures) provides verbal and/or hands-on assistance as necessary and takes over if the participant cannot complete the procedure or if any concerns regarding patient safety arise.

### Outcome Measures

The primary outcome measure is the difference in performance between the control and intervention groups during participants’ 2 clinical colonoscopies. Each videotaped clinical colonoscopy will be independently assessed by 2 experienced endoscopists using the Joint Advisory Group for GI Endoscopy Direction Observation of Procedural Skills (JAG DOPS) (Multimedia Appendix 4) [15]. The raters will be blinded to the group assignment. Training on how to use the tool will be provided for raters by the investigators of the study.

Secondary outcome measures include the differences between the control and intervention groups with respect to (1) procedural knowledge, as assessed by the knowledge MCQ tests; (2) NTS performance during the clinical colonoscopies, as assessed by the Modified Objective Structured Assessment of Non-Technical Skills (M-OSANTS) for colonoscopy, which has been previously validated for surgery and modified for endoscopy [4] (Multimedia Appendix 5); (3) clinical performance on clinical colonoscopies, as assessed by the Gastrointestinal Endoscopy Competency Assessment Tool (GiECAT) [16] (Multimedia Appendix 6); (4) technical performance on a VR simulated colonoscopy after training and 4 to 6 weeks after training (immediate and delayed post-training assessments, respectively), as assessed by the JAG DOPS and the GiECAT; (5) technical and non-technical performance during an integrated scenario format test 4 to 6 weeks after training, as assessed by the JAG DOPS, GiECAT, and M-OSANTS; (6) patient comfort during the clinical colonoscopies, as assessed by the Nurse-Assessed Patient Comfort Score (NAPCOMS) [17] (Multimedia Appendix 7); (7) participant self-efficacy, as measured by an adapted scale based on the General Self-Efficacy Scale (GSE) [18,19] (Multimedia Appendix 8); and (8) global performance and communication skills during integrated scenarios as assessed by the Integrated Scenario Global Rating Form (ISGRF) and Integrated Scenario Communication Rating Form (ISCRF) [11,20,21], respectively (Multimedia Appendices 9 and ).

Experienced endoscopists will assess participants’ colonoscopy-specific skills, technical skills, and NTS during the pre-training, immediate, and delayed post-training simulation-based assessments.

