#### Non-Technical Performance

Non-technical performance on the simulator for each group will be determined by comparing the scores from the M-OSANTS, ISGRF, and ISCRF. Specifically, a mixed factor 2 (control curriculum versus intervention curriculum) times 3 (pre-test, post-test, delayed test) ANOVA will be used to determine whether there is a difference based on the rating scales. The Tukey HSD test will be used as a post-hoc analysis to determine any significant differences.

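### Outcome 5 is a between-arm difference at 4 to 6 weeks, but neither omnibus term of the planned 2 x 3 ANOVA tests that difference, and the Tukey follow-up tests it weakly

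*Protocol article*

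**What the plan says.** Under Outcome Measures, outcome 5 is "technical and non-technical performance during an integrated scenario format test 4 to 6 weeks after training", assessed with JAG DOPS, GiECAT and M-OSANTS. Outcome 4, in the same list, names both occasions: "technical performance on a VR simulated colonoscopy after training and 4 to 6 weeks after training (immediate and delayed post-training assessments, respectively".

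The integrated scenario is also run straight after training. The Post-Test section lists it as a measure of "NTS acquisition (VR simulation-based integrated scenario test"), and Outcome Measures confirms that endoscopists rate "technical skills, and NTS during the pre-training, immediate, and delayed post-training simulation-based assessments". The Delayed Testing section gives the later test a different purpose: "to compare retention and transfer of skill between the control and intervention groups".

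For the analysis, the Non-Technical Performance section says "Non-technical performance on the simulator for each group will be determined by comparing the scores from the M-OSANTS, ISGRF, and ISCRF", by a mixed 2 (curriculum) "times 3 (pre-test, post-test, delayed test) ANOVA will be used to determine whether there is a difference based on the rating scales". Tukey HSD follows as the post-hoc step. The Technical Performance section sets out the same model and post-hoc test for simulator DOPS and GiECAT.

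**The concern.** The protocol separates two questions: whether the skill was acquired (immediate test) and whether it was retained (delayed test). Outcome 5 as worded belongs to the second. The planned analysis spans three occasions, and its stated aim is only to find whether there is a difference. A 2 x 3 model gives a group main effect and a group-by-time interaction, and neither equals the arm difference at the delayed test.

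Two things are at stake. First, a significant omnibus result could be reported under an outcome that means retention, although it says nothing specific about 4 to 6 weeks. Second, if the delayed difference is real, the stated route to it is a multiple-comparison step over cell means, which costs power that a single named contrast would keep.

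**Working it through.** **Inputs.** Group sizes of 19 and 23 (Results), alpha .05 (Analysis Plan) and three test times come from the article. The effect size (1.0 SD), the between-visit correlation ρ (0.3, 0.5, 0.7), equal SDs and compound symmetry are assumptions.

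**The plan's own figure.** The stated N of 16 is a between-factors calculation with f=0.65 and 3 measurements. Taking ρ=0.5, the noncentrality is f²·N·m/(1+(m−1)ρ) = 0.4225 × 16 × 3 / 2 = 10.14 on 1 and 14 df, which gives power 0.841. The figure reproduces and is not in dispute. It concerns an effect averaged over the measurements, not one at the delayed test.

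**What each term estimates.** Write the arm differences at pre-test, post-test and delayed test as (δ1, δ2, δ3). Outcome 5 is δ3.
- Main effect: (δ1+δ2+δ3)/3. Randomization makes δ1 zero in expectation, so a lasting 1.0 SD effect (0, 1, 1) appears as 0.67 SD and an immediate-only effect (0, 1, 0) as 0.33 SD.
- Interaction: driven by Σ(δj − mean δ)². For (0, 1, 0) this is 1/9 + 4/9 + 1/9 = 6/9. For (0, 1, 1) it is 4/9 + 1/9 + 1/9 = 6/9. The two patterns have the same noncentrality, so the interaction F test has the same power for a vanished effect as for a retained one.

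**Effect at the immediate test only (true delayed difference zero).** The standard error of a difference at one visit is √(1/19 + 1/23) = 0.310 SD. For the main effect it is 0.310 × √((1+2ρ)/3) = 0.226, 0.253 and 0.277 SD. The expected 0.333 SD is then 1.47, 1.32 and 1.20 standard errors. Simulation with 20,000 trials per setting gives:

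| ρ | Main effect significant | Interaction significant | Direct delayed comparison significant |
|---|---|---|---|
| 0.3 | 30% | 80% | 5% |
| 0.5 | 25% | 92% | 5% |
| 0.7 | 22% | 99% | 5% |

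The interaction rejections are correct, because the arms do differ over time. They simply do not show a difference at 4 to 6 weeks.

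**Lasting effect of 1.0 SD.** A direct t-test at the delayed visit has noncentrality 1.0/0.310 = 3.23 on 40 df and critical value 2.02, so power is about 88%. For Tukey HSD, take all six cell means with pooled cell variance and 40 df (an assumed reading, since the article does not say which means are compared). The critical studentized range is 4.23, equivalent to |t| = 4.23/√2 = 2.99, and power falls to about 59%. In observed differences, the threshold rises from 2.02 × 0.310 = 0.63 SD to 2.99 × 0.310 = 0.93 SD.

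**Pre-test adjustment.** Under the same assumptions, adjusting the delayed score for the pre-test score multiplies its residual variance by 1 − ρ², that is 0.91, 0.75 or 0.51, so the direct contrast gains further.

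**The case against.** The strongest reply is that the model contains what is needed. Time is a factor, so visits are not simply pooled: only the main effect averages over them, the interaction lets the arm difference vary, and Tukey HSD can then locate an effect at a visit. This stands. Under the six-cell reading, an immediate-only effect would yield a falsely significant delayed Tukey contrast in under 1% of trials. A reader might infer that the plan will usually present a short-lived effect as retention, because main effect or interaction is significant in 86-99% of trials in the immediate-only setting against 5% for the delayed comparison. The documents do not support that. Most of those rejections are correct interaction findings, and a false retention claim would need someone to report an omnibus p-value as a delayed difference.

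A reader might also infer that the immediate result is hidden and could be promoted or dropped at will. That is too strong as well. The immediate test is openly planned in the Post-Test section, its ratings in Outcome Measures and its analysis in Non-Technical Performance. Outcome 8 covers integrated scenarios by ISGRF and ISCRF with no time limit. Only the immediate integrated-scenario M-OSANTS, DOPS and GiECAT scores fall outside the listed outcomes.

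Finally, a journal article may leave the choice of contrast to an analysis plan. Silence on that would indeed be no finding. Here, though, the article states both a single-visit outcome and an analysis for it, and the two do not match. Choosing a delayed-only outcome is itself legitimate.

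**Conclusion.** The mismatch holds and is moderate. Outcome 5 is declared at one visit, and neither omnibus term of the stated analysis tests the difference at that visit. The stated post-hoc step can reach it, but under the six-cell reading with about 59% power rather than about 88% for a lasting 1.0 SD effect. For an effect confined to the immediate test, a significant main effect (22-30%) or interaction (80-99%) would not be evidence of retention.

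These sizes rest on the assumed effect, correlations of 0.3 to 0.7, equal SDs and compound symmetry; the Tukey figure also rests on how that step is read. The textual mismatch depends on none of them. Outcome 5 is one of eight secondary outcomes, and the primary outcome, clinical JAG DOPS, is not affected.

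**What to change.** State that outcome 5 is answered by the between-arm difference at the delayed test, with its 95% confidence interval, for each of DOPS, GiECAT and M-OSANTS in the integrated scenario, preferably adjusted for the pre-test score already collected. Let only that contrast support a claim about 4 to 6 weeks. The 2 x 3 ANOVA can stay as a description of the course over time.

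Report the immediate between-arm difference separately and call it acquisition. Either reword outcome 5 to name both occasions, as outcome 4 does, or keep it delayed-only and label the immediate difference supportive. Both are acceptable.

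The cost is a few sentences and one more reported secondary contrast per scale, with no new data. The Results section describes ratings and analysis as still to be completed, so on the documents the contrast could be fixed before results are known.
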